## Methods/design

### Study design

In this multisite randomized controlled trial, we will evaluate the effects of the START intervention on ART adherence and HIV virologic suppression. We will recruit 240 patients with HIV at two HIV clinics, with each randomized to receive either START or usual care at a 1:1 ratio at each clinic (60 patients in each arm at each site). Random assignment codes will be computer-generated and placed in a sequential list that will be maintained by the principal investigator. Assignments will be issued to study coordinators once candidates have enrolled and completed the baseline survey. The randomization will be stratified by prior ART history (naïve or experienced) and CD4 count (<350 vs. ≥350 cells/mm^3^) because of the influence that prior ART history may have on adherence and clinical outcomes, and also due to our interest in determining whether early-stage patients can adhere as well as other patients to treatment. There is no way to blind the participants to whether they are receiving the intervention; this could potentially influence adherence performance and retention, as clients may feel more or less incentive to perform well in light of whether they receive the intervention. We do not see a way to prevent this potential bias, nor do we have a way to distinguish such effects from actual intervention effects; however, this limitation will be cited in reports of study findings.

Primary outcomes will be optimal dose-taking adherence (>85 % prescribed doses taken), as measured with electronic monitoring caps, and undetectable HIV viral load. Secondary outcomes will include dose-timing adherence (>85 % prescribed doses taken on time) and CD4 count. Primary endpoints will be month 6 (short-term effect) and month 24 (to test durability of effect), though electronic monitoring will be continuous and a fully battery of assessments will be administered every 6 months for 24 months. See Fig. 1 for the flow of participant procedures through the protocol. Participants will be paid $30 for each completed assessment, as well as a $50 bonus if they complete all five primary assessments and $10 for each attended intervention session. To limit attrition, contact information will be collected at enrollment and verified at each follow-up visit. Furthermore, the study coordinator will check with all study participants at the midway point between surveys, which will be timed to coincide with regular scheduled clinic appointments.

**Fig. 1 Fig1:**
[figure not shown]
Flowchart of study protocol. *RZ* randomized, *ART* antiretroviral therapy, *MEMS* Medication Event Monitoring System

The study protocol has been reviewed and approved by institutional review board (IRB) at the University of California, Los Angeles (UCLA), and a certificate of confidentiality has been obtained from the National Institute of Mental Health. Any protocol modifications will be submitted to the IRB for review, and participants will be informed if warranted. The trial is registered with the National Institutes of Health (NIH) ClinicalTrials.gov registry and assigned the number NCT02329782.

### Setting

The study will take place at St. Mary’s Comprehensive AIDS Resource and Education Clinic in Long Beach, CA, USA, and UCLA Clinical AIDS Research and Education (CARE) Center. The St. Mary’s clinic serves over 1500 clients with HIV, of whom about 60 % are nonwhite and 85 % are male. The UCLA CARE center has nearly 1300 clients with HIV, of whom 83 % are male and 40 % are nonwhite. Both clinics have highly productive research units that conduct primarily biomedical and therapeutics research. Both research units have highly trained study coordinators who are experienced in research ethics, evaluation procedures, protocol implementation, and provision of adherence treatment support and counseling (as part of research trials, not usual care), and they will be trained to be the project’s site coordinators and intervention counselors.

### Study sample

Eligibility criteria include (1) patient and provider plan to start or restart (not currently on ART) the patient on ART; (2) patient has stable health status and no acute opportunistic infections or medical conditions (including acute HIV infection) that warrant starting ART immediately, as determined by the patient’s provider; (3) detectable HIV viral load at last test (within past 6 months); (4) if CD4 count is <200 cells/mm^3^, patient is on prophylactic medication to limit risks associated with the intervention’s imposed delay in starting ART; (5) patient is age 18 years or older; and (6) patient speaks English. Providers will inform eligible patients of the study, and patients who interested in participating will be referred to the study coordinator for consent procedures, eligibility screening, baseline survey, and randomization. Written informed consent will be obtained from all participants at enrollment. For control patients, the baseline visit is scheduled for the same day or within 1 week of the screening assessment. The baseline visit for intervention patients will take place on the same day as the last pretreatment intervention session (once they achieve >85 % dose-taking adherence during a practice trial).

We calculated the size of effects that this sample can detect with 80 % power (two-tailed test) with regard to the primary outcomes. On the basis of the pilot study [14], we expect that 40 % of the control group will achieve optimal (>85 %) dose-taking adherence and 45 % will achieve undetectable viral load. With these expected rates in the control group, together with estimates of 10 % and 30 % attrition at months 6 and 24, respectively, our sample size of 240 will be powered to detect a 9 % difference between the two arms with regard to both optimal dose-taking adherence and undetectable viral load at both months 6 and 24.

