##### Pretreatment training phase

This phase is composed of a series of up to four 1-week practice trials accompanied by adherence counseling and a dose regulation mechanism in which patients discontinue the practice trials and initiate ART once >85 % dose-taking adherence is achieved in a single practice trial, thus demonstrating adherence readiness. Using 85 % adherence to define readiness is consistent with what the literature indicates is needed for optimal treatment benefits with the new, more potent ART regimens [1–3]. With today’s common once-daily regimens, this threshold allows the patient to miss one dose over the course of the week and still meet the criteria for readiness. Early exercises and sessions will be focused on enhancing motivation and confidence to help prepare the patient for later skill-building exercises that may call for behavior change to overcome adherence barriers.

***Session 1*** Following an introduction and description of the ART regimen, the counselor will provide education about concepts such as viral load, drug resistance, and the importance of dose-timing to ensuring a constant adequate drug level. The importance of being ready to adhere well before starting treatment will be emphasized. Motivational interviewing (MI) techniques [16] will be used to help the patient develop or strengthen positive attitudes toward treatment and adherence, with the goal of improving adherence self-efficacy and motivation to adhere well. Exercises will be devoted to enhancing social support (reminders, transportation to clinic, provide reinforcement for successful adherence) provided by the patient’s social network. The practice trial will be introduced as an opportunity to experience what it is like to follow the prescribed ART regimen and to evaluate the patient’s readiness to start treatment. The practice trial regimen will mimic what the patient’s provider intends to prescribe. A 1-week supply of vitamins, with the electronic monitoring cap attached to one of the pill bottles, will be given to the patient to complete over the coming week.

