### Measures

Below are descriptions of the primary and secondary outcomes with regard to ART adherence, virologic suppression, immune function and HIV care retention (see Table 2). The survey assessment includes measures of potential mediators of intervention effects (e.g., components of the IMB model such as HIV knowledge, adherence motivation and self-efficacy, as well as depression and substance use), and potential moderators (e.g., demographics), but these are not described in detail here; however, we do describe below our survey measures of adherence support received from HIV providers as part of usual care. The survey will be facilitated using computer-assisted self-interview technology, which automatically stores survey responses; survey data files will be stored on password-protected, encrypted files.

**Table 2 Tab2:** Primary and secondary outcomes

Outcome measures	Outcomes
Primary outcomes	
HIV viral load (chart-abstracted HIV RNA)	Undetectable viral load (binary) (primary) Log change in viral load from baseline (continuous)
Dose-taking adherence (MEMS)	Took at least 85 % of prescribed doses (binary) (primary) Percentage of prescribed doses taken (continuous)
Secondary outcomes	
Dose-timing adherence (MEMS)	Percentage of prescribed doses taken in correct time window (±2 h for twice-daily regimens and ±3 h for once-daily regimens) (continuous) Took at least 85 % of prescribed doses on time (binary)
Dose-taking adherence (self-report)	Percentage of prescribed doses taken in past 7 days (continuous) Took at least 85 % of prescribed doses (binary) Visual analogue scale rating from 0 % to 100 % adherence over past 30 days
Dose interruptions (MEMS data)	Number of >48-h interruptions
Clinic attendance (chart abstract; self-report)	Number of attended and missed clinic appointments in past 6 months
CD4 count (chart-abstracted)	Change from baseline

*MEMS* Medication Event Monitoring System

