### Data analysis

The primary aim of the analysis is to determine whether the START intervention is superior to usual care in helping patients achieve optimal adherence and virologic suppression in both the short and long term. Dose-taking adherence and viral load are the primary outcomes. Continuous adherence will be assessed for normality and transformed if needed; viral load data will be log-transformed. Our primary analysis is based on an intent-to-treat approach, with secondary analyses involving study completers. Attrition weights will be used to account for dropouts, and all analyses will incorporate design effects from this weighting in the calculation of standard errors and tests of significance. Analyses will be conducted to compare groups at months 6 and 24 to assess short- and long-term effects.

In addition to simple between-group comparisons at each time interval (baseline and months 6, 12, 18, and 24), we will conduct analysis of the trajectory of outcomes. Longitudinal analyses will be performed, using mixed effects models to examine differences in trajectories of adherence and HIV viral load across the two groups, controlling for patient characteristics. Linear mixed effects models will be used for continuous outcomes, while nonlinear mixed effects models will be used for binary outcomes (e.g., took at least 85 % of prescribed doses, undetectable viral load). Along with a fixed linear term for time, a random subject-specific intercept will be incorporated, with the appropriate covariance structure of the repeated measures being determined during analysis. Covariates added to the models will include components of our conceptual IMB framework and intervention (e.g., HIV knowledge, adherence motivation, adherence self-efficacy), as well as correlated process variables (e.g., number of practice trials completed, total number of sessions attended). To adequately model longitudinal HIV viral load, which has a high proportion of values below the limit of detection, a Bernoulli/log-normal random effects mixture model with left censoring will be used [18, 19]. Analysis of covariance will be used to define an effect size estimate in the analysis of the primary outcomes and to provide baseline adjustment to improve statistical power.

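### The protocol puts baseline before randomisation in one place and, for START patients only, after counselling and a passed practice trial in another; the analysis baseline must be named

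*Protocol article*

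**What the plan says.** All references are to the protocol article.

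**Baseline before randomisation.** Study design: "Assignments will be issued to study coordinators once candidates have enrolled and completed the baseline survey". Study sample gives the same order for referred patients: "consent procedures, eligibility screening, baseline survey, and randomization".

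**Baseline by arm.** Later in the same paragraph of Study sample: "For control patients, the baseline visit is scheduled for the same day or within 1 week of the screening assessment". Then, for START: "The baseline visit for intervention patients will take place on the same day as the last pretreatment intervention session", qualified as "once they achieve >85 % dose-taking adherence during a practice trial".

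**What precedes the START visit.** Pretreatment training phase: "This phase is composed of a series of up to four 1-week practice trials accompanied by adherence counseling". The section Usual clinical care states that controls get neither structured counselling nor practice trials.

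**How baseline is used.** Data analysis plans between-group comparisons at baseline and at months 6, 12, 18 and 24, and an analysis of covariance to "provide baseline adjustment to improve statistical power". It also names HIV knowledge, motivation and self-efficacy as model covariates. Table 2 lists log change in viral load and change in CD4 count, both from baseline. The primary analysis is intent-to-treat.

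**The concern.** A baseline value is useful because assignment cannot have influenced it. The START visit rule breaks that condition in three ways: the visit follows randomisation, it follows part of the intervention, and it is tied to success in a task that controls never perform.

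If the survey data from that visit are used as baseline, a difference between arms may be an early effect of counselling and not chance imbalance. Adjusting for a measure that START has already raised would remove whatever part of the treatment effect runs through it. A baseline that exists only for some START patients also sits badly with an intent-to-treat analysis, because the missing values would belong to the patients who did worst in the practice trials or left early.

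**Working it through.** The plan states no figure on this point, so the check is mainly textual, with one illustrative calculation.

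**1. Can one assessment satisfy both accounts?** For controls, yes: a visit on the screening day or within a week can precede randomisation. For START, no: practice trials exist only in that arm, so a visit held after passing one must follow randomisation.

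**2. One baseline or two?** Study design pays a bonus for completing all five primary assessments. Data analysis lists baseline plus four follow-ups, and 1 + 4 = 5. This points to a single baseline assessment, although the article never says whether the survey and the visit are the same thing.

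**3. Exposure by the START visit.** Session 1 precedes the first practice week, and one further session follows each of 1 to 4 practice weeks. Sessions by that day: 1 + 1 = 2 up to 1 + 4 = 5, over about 1 to 4 weeks. This counts the session held on the visit day itself; the article does not say whether the assessment comes before or after it. Controls have no sessions and wait 0 to 1 week from screening. Table 1 shows that START sessions work on information, motivation and self-efficacy. Measures lists the corresponding survey constructs as potential mediators.

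**4. Which variables are exposed?**
- *Knowledge, motivation, self-efficacy:* directly targeted by the sessions.
- *Viral load and CD4:* abstracted from routine charts. During practice trials patients take vitamins, not ART, so these values should hardly move. What can differ is the date of the value chosen as baseline.
- *Binary primary outcomes:* not change scores, so baseline reaches them only through adjustment.

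**5. Who might lack the START visit?** The section on Sessions 2–5 leaves the ART decision for patients who fail four trials to patient and provider, and mentions no baseline visit. No rule covers patients who leave during pretreatment.

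As a guide to scale, take a once-daily regimen, where a week is passed with at least 6 of 7 doses (6/7 = 85.7%). Assume independent doses with constant per-dose adherence *p*. The protocol does not give *p*.

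Pass one week: q = 7p⁶(1 − p) + p⁷. Never pass in four weeks: (1 − q)⁴. START arm: 2 sites × 60 = 120.

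| Assumed p | q | (1 − q)⁴ | Of 120 |
|---|---|---|---|
| 0.6 | 0.159 | 0.501 | about 60 |
| 0.7 | 0.329 | 0.202 | about 24 |
| 0.8 | 0.577 | 0.032 | about 4 |
| 0.9 | 0.850 | 0.0005 | about 0 |

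Counselling between trials is meant to raise adherence, so a constant *p* probably overstates failure for a patient who starts low. Patients who leave early are not counted.

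**The case against.** The best defence is that the survey and the visit are two different things. On that reading the survey is taken before randomisation in both arms, as stated twice, and the visit marks the start of ART. This is coherent: ART is prescribed at the session where the practice trial is passed, and the objective counts months 6 and 24 from ART start. The survey baselines would then be comparable. Fig. 1, which is not available here, may show the sequence. This defence stands as far as it goes: it is not established that baseline differs by arm. It does not remove the need to act, because the article never separates the two terms, its count of five assessments points to one baseline, and it does not say which one the analysis uses.

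Some stronger inferences are tempting and are not supported:

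- *Patients who never pass have no baseline.* The main clause refers to the last pretreatment session, and a patient who fails four trials still has a fifth session. The visit is unclear for them, not certainly absent.
- *Such patients are dropped.* No text makes the visit a condition of analysis, and the stated approach is intent-to-treat with attrition weights.
- *Viral load and CD4 change scores are distorted by counselling.* There is no evident route before ART.
- *Adjustment would erase the effect.* That needs the adjusted measure to carry the whole effect. The covariance analysis does not name its covariates, and nothing in the article supports full mediation.

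**Conclusion.** The point holds as a contradiction about when baseline is measured, with a real consequence if the visit rule is the one followed. In that case START survey measures are taken after randomisation and after 2 to 5 sessions, and comparisons at baseline or adjustment for those measures are treatment-affected. The likely direction is loss of part of the effect on adjustment, provided counselling raises these measures and they carry some of the effect. The article gives no basis for a size.

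For viral load and CD4 the consequence is mainly a timing difference of a few weeks. The number of START patients for whom the visit is unclear is unknown and could be anything from negligible to large: near 0 at 90% assumed adherence and about half at 60%, under independent once-daily doses. If the survey and the visit are separate and the survey is the analysis baseline, the problem reduces to wording.

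**What to change.** 1. Reconcile the Study design and Study sample sections so that each assessment has one name and one time.
2. Define baseline in both arms as the survey completed before randomisation and the last chart viral load and CD4 count before randomisation. Use only these for baseline tables, change scores and baseline covariates.
3. Give the later START visit another name and do not use its data as baseline.
4. State that no randomised patient is excluded from the analysis for lacking that visit.

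The cost is mostly wording. The text already calls for a survey before assignment. Eligibility requires a viral load result from the past 6 months, and stratification by CD4 count requires a value at randomisation. One downside is that START change scores span a few more weeks, because ART starts after the practice phase.

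Enrolment is active, so the sites' actual order should be checked now. If any START patient had the survey only at the later visit, the pre-randomisation survey values cannot be recovered, whereas the chart values can.

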Most ART adherence interventions are designed to help patients achieve and maintain adherence readiness, but few target patients before they start treatment or tailor the amount of adherence support [12]. The Supporting Treatment Adherence Readiness through Training (START) intervention is based on the information-motivation-behavioral skills (IMB) model of behavior change [13]. It includes (1) brief pill-taking practice trials for enhancing pretreatment adherence counseling and providing a behavioral criterion for determining adherence readiness and the timing of treatment initiation and (2) a performance-driven dose regulation mechanism to tailor the amount of counseling to the individual needs of the patient and conserve resources. In a pilot randomized controlled trial [14], START had effects on both behavioral adherence and virologic suppression, unusual even for effective ART adherence interventions, which have typically improved one but not both of these outcomes [15]. The small sample size (*N* = 54) precluded adequate statistical power, but effect size estimates were 0.22 (dose-taking adherence), 0.75 (dose-timing adherence), and 0.41 (complete virologic suppression) over the first 6 months of treatment, with the latter two far exceeding the average 0.19 effect size found in a recent meta-analysis of ART adherence interventions that, like START, were not focused solely on patients already demonstrating adherence problems [12]. These promising results provide the rationale for the current, more rigorous, larger controlled trial of START.

In the present study, we are evaluating the effects of the START intervention on the primary outcomes of dose-taking adherence and undetectable viral load in a multisite randomized controlled trial, the protocol of which this article describes in detail. The primary objective of the study is to determine whether START is superior to usual care in helping patients achieve optimal (>85 %) dose-taking adherence, and complete viral suppression (undetectable HIV viral load) 6 months (short-term efficacy) and 24 months (long-term efficacy) after starting ART.

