## Discussion

In this study, we will conduct a rigorous, controlled evaluation of the innovative ART adherence intervention START. Unlike most other ART adherence interventions that target people who are already on ART [12, 15, 20], START attempts to provide the field with an evidence-based intervention that works with patients before they start treatment to ensure adherence readiness before initiation—an approach that is particularly timely as more patients with early stage disease start ART and may be less ready to adhere well.

An added innovation of START is highlighted in its design, which features components that are lacking in most ART adherence interventions to date: (1) inclusion of pretreatment, early-treatment, and ongoing maintenance training phases; (2) use of brief practice trials for determining adherence readiness and the timing of ART initiation; and (3) inclusion of a dose regulation mechanism that adjusts the amount of pretreatment and maintenance training based on the patient’s recent adherence performance. START combines these features with a goal of producing a robust and lasting effect on both adherence and clinical outcomes, as well as to be sensitive to and consistent with community practice, the limited resources available to most clinics and providers (especially as more patients start ART), and the wide range of adherence skills present among patients. This flexibility and attention to individual patient needs should increase the acceptability of the program to patients, providers, and clinic administrators, thus improving the likelihood of future translation into usual care.

Our pilot controlled trial of START revealed evidence of the intervention’s potential promise, with medium to large effects on both behavioral adherence and undetectable viral load [14]. If this larger, fully powered controlled test of the intervention produces similar results, START will provide clinics with a model for a “new-generation” adherence support program to assist their patients in achieving optimal treatment outcomes. Also, this may be the first study of an adherence intervention with a 2-year intervention and follow-up period, which will enable us to assess the intervention’s long-term efficacy.

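### The stated inputs do not give a detectable difference of 9 points with 240 patients; at two-sided 5% they give about 19 points at month 6 and 21.5 at month 24

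*Protocol article*

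**What the plan says.** The Study sample section fixes the sample and solves for the effect: "We calculated the size of effects that this sample can detect with 80 % power (two-tailed test"). For the control arm it says "we expect that 40 % of the control group will achieve optimal" dose-taking adherence and that 45% will reach undetectable viral load. It assumes attrition of 10% at month 6 and 30% at month 24. It concludes that "our sample size of 240 will be powered to detect a 9" per cent "difference between the two arms with regard to both optimal dose-taking adherence and undetectable viral load at both months 6 and 24". Alpha is not given.

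The Study design section gives the allocation: patients are enrolled at two clinics, "with each randomized to receive either START or usual care at a 1:1 ratio at each clinic", which makes 120 per arm in total. The Discussion then refers to "this larger, fully powered controlled test of the intervention".

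**The concern.** A two-arm comparison of proportions near 40% to 50% with about 100 patients per arm has a standard error of roughly 7 points. A difference needs to be about 2.8 standard errors to be detected with 80% power at two-sided 5%. That is near 19 points, about twice the printed figure.

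The figure is the article's only justification of the sample size, and it covers both primary outcomes at both primary endpoints. A reader who takes it at face value will believe that the trial can reliably show a benefit of 9 points. The approximate half-width of a 95% confidence interval for the difference is 1.96 × √(2 × 0.25/108) = 13 points at month 6 and 1.96 × √(2 × 0.25/84) = 15 points at month 24. A non-significant result would therefore often be compatible with a benefit of 9 points.

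**Working it through.** **Inputs**

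| Input | Value | Source |
|---|---|---|
| Randomised | 240, 1:1, so 120 per arm | Study design |
| Control rate, dose-taking adherence | 40% | Study sample |
| Control rate, undetectable viral load | 45% | Study sample |
| Attrition | 10% (month 6), 30% (month 24) | Study sample |
| Power, sidedness | 80%, two-tailed | Study sample |
| Alpha | 0.05 two-sided | Assumption; not stated |

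Analysed per arm: 120 × 0.90 = 108 at month 6; 120 × 0.70 = 84 at month 24.

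**Formula.** Two-proportion z-test with pooled null variance. With d = p₂ − p₁ and p̄ = (p₁ + p₂)/2,

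power = Φ{ [d√n − 1.96 √(2p̄(1 − p̄))] / √(p₁(1 − p₁) + p₂(1 − p₂)) }.

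**Trying to reproduce 9 points.** For 40% against 49%, √(2p̄(1 − p̄)) = 0.703 and √(p₁(1 − p₁) + p₂(1 − p₂)) = 0.700.

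- Month 6: (0.09 × √108 − 1.96 × 0.703)/0.700 = (0.935 − 1.377)/0.700 = −0.63, so power is 26%.
- Month 24: (0.09 × √84 − 1.377)/0.700 = (0.825 − 1.377)/0.700 = −0.79, so power is 21%.

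The stated 80% is not reproduced.

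**Difference that does give 80% power**

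| | Control 40% | Control 45% |
|---|---|---|
| Month 6, 108 per arm: detectable difference | 19.0 points | 18.9 points |
| Month 6: power for 9 points | 26.4% | 26.1% |
| Month 24, 84 per arm: detectable difference | 21.5 points | 21.3 points |
| Month 24: power for 9 points | 21.5% | 21.3% |

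Check at month 24: for 40% against 61.5%, (0.215 × √84 − 1.96 × 0.707)/0.690 = 0.85, which is 80% power.

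**Sample size that 9 points would need.** n per arm = [1.96 √(2p̄(1 − p̄)) + 0.842 √(p₁(1 − p₁) + p₂(1 − p₂))]² / d².

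- From 40%: (1.377 + 0.589)² / 0.0081 gives 478.
- From 45%: (1.386 + 0.593)² / 0.0081 gives 484.

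Randomised, that is 956/0.9 = 1,063 to 968/0.9 = 1,076 with 10% attrition, and 956/0.7 = 1,366 to 968/0.7 = 1,383 with 30%.

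**Sensitivity to what is not stated**

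- Two-sided alpha 0.20: detectable difference 14.4 points at month 6 and 16.3 at month 24.
- No attrition (120 per arm) at 0.05: 18 points.
- Arcsine formula, from 40%: 18.9 and 21.4 points. Continuity correction, from 40%: 19.9 and 22.6 points.
- To reach 80% power for 9 points, two-sided alpha would have to be roughly 0.6 at month 6 and 0.7 at month 24.

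**The case against.** The best defence is that the article condenses a fuller calculation. Alpha is unstated, and the Data analysis section plans baseline adjustment and longitudinal mixed models, either of which can improve on a plain comparison of proportions. That is fair as a caution, and it is why 0.05 is labelled here as an assumption. It does not recover 9 points.

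- Baseline covariates would have to explain 1 − (9/18.96)² = 77% of the outcome variance at month 6 and 1 − (9/21.46)² = 82% at month 24. Eligibility requires a detectable viral load and no current ART, so baseline values of the two binary outcomes can explain little.
- The power claim concerns the difference at each of two months. Even four fully independent measurements per patient give 9.5 points at month 6 and 10.7 to 10.8 at month 24.
- Reading 9% as a relative difference makes matters worse: 40% against 43.6% needs 2,946 per arm, and 45% against 49.05% needs 2,383.

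Four stronger readings are tempting, and the article does not support them.

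- A reader might infer that one figure cannot serve both months because the month 24 sample is smaller. It can, if 9% is meant as the month 24 limit; the larger month 6 sample would then also suffice. The fault is the size of the figure.
- A reader might try to say how 9% arose. The article does not show it, and no explanation can be proved.
- A reader might compute power for the pilot effects ("effect size estimates were 0.22 (dose-taking adherence), 0.75 (dose-timing adherence), and 0.41 (complete virologic suppression"). The Background does not define the effect-size metric or say whether 0.22 refers to the binary outcome, so such powers rest on a guess.
- A reader might take the Discussion's "medium to large effects on both behavioral adherence and undetectable viral load" as contradicted by the 0.22. Behavioural adherence can include dose-timing, for which the pilot effect was 0.75, so this is not a contradiction.

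**Conclusion.** The stated detectable difference is wrong as written. On the article's own inputs and an assumed two-sided alpha of 0.05, the trial has 80% power for about 19 points at month 6 and 21.5 (from 40%) or 21.3 points (from 45%) at month 24. Power for 9 points is about 26% and 21%. The exact values depend on the assumed alpha, but the conclusion does not: neither removing attrition nor relaxing alpha to 0.20 brings the detectable difference near 9. The results also leave out the design effect of the attrition weights, which the Data analysis section says will enter the standard errors and which would widen the gap. Because this is the article's only sample-size justification and it covers the primary comparisons, it should be corrected. The description of the trial as fully powered holds only for differences of the larger size.

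**What to change.** State alpha and replace the last sentence of the power paragraph with wording such as:

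> With 108 per arm at month 6, the trial has 80% power (two-sided 5%) to detect a difference of about 19 percentage points (40% to 59%; 45% to 64%). With 84 per arm at month 24, it has 80% power to detect about 21.5 points (40% to 61.5%; 45% to 66.3%). These figures are before the design effect of the attrition weights.

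If 9% came from a different method, disclose that method and every input needed to reproduce it. In the Discussion, qualify the phrase about full power by giving the size of difference to which it applies.

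This is a change of wording only. Enrolment, conduct and analysis stay as planned; the cost is a less favourable stated figure.
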